**Table S18: Pre-COVID-19 Subgroup Analyses at Baseline and 3 Months**

|                                                                                                                    | Control
(n=22)
Mean (95%CI)            | Strategy 1
(n=45)
Mean (95%CI)         | Strategy 2
(n=42)
Mean (95%CI)         | Primary Comparison (CI)
Strategies 1 and 2 vs.
Control
(N=109) | P-value | Secondary
Comparison (CI)
Strategy 2 vs. 1
(N=87) | P-value |
|--------------------------------------------------------------------------------------------------------------------|----------------------------------------------|----------------------------------------------|----------------------------------------------|-------------------------------------------------------------------------|---------|------------------------------------------------------------|---------|
| DASH Scorea
At baseline
At 3 months
Change (baseline to 3 months)                       | 45.1 (39.9, 50.4)
48.9 (43.6, 54.2)       | 42.6 (38.6, 46.6)
53.2 (49.2, 57.2)       | 42.7 (38.4, 47.0)
56.4 (52.1, 60.7)       | 8.3 (3.4, 13.3)                                                         | 0.001   | 3.1 (-1.3, 7.6)                                            | 0.17    |
| Systolic blood pressurea - mm Hg
At baseline
At 3 months
Change (baseline to 3 months)  | 133.9 (123.3, 144.5)
132.2 (121.5, 142.8) | 134.1 (125.3, 142.9)
124.9 (116.1, 133.7) | 128.9 (119.3, 138.4)
123.7 (114.1, 133.3) | -5.4 (-12.0, 1.2)                                                       | 0.11    | 4.0 (-1.9, 10.0)                                           | 0.18    |
| Diastolic blood pressurea – mm Hg
At baseline
At 3 months
Change (baseline to 3 months) | 87.5 (80.2, 94.9)
85.7 (78.4, 93.0)       | 85.1 (79.0, 91.2)
80.7 (74.6, 86.8)       | 85.2 (78.6, 91.9)
83.1 (76.5, 89.8)       | -1.4 (-5.2, 2.5)                                                        | 0.48    | 2.3 (-1.2, 5.7)                                            | 0.19    |
| BMIa
At baseline
At 3 months
Change (baseline to 3 months)                              | 34.5 (28.2, 40.8)
34.3 (28.0, 40.6)       | 37.2 (32.0, 42.4)
36.7 (31.5, 41.9)       | 35.1 (29.3, 40.8)
34.3 (28.6, 40.1)       | -0.4 (-0.9, 0.1)                                                        | 0.11    | -0.3 (-0.7, 0.2)                                           | 0.28    |
| Non-HDL-Ca - mg/dl
At baseline
At 3 months
Change (baseline to 3 months)                | 113.0 (93.3, 132.7)
116.0 (96.2, 135.7)   | 122.3 (106.4, 138.2)
117.8 (101.9, 133.7) | 118.5 (101.7, 135.3)
121.0 (104.2, 137.8) | -4.0 (-16.3, 8.4)                                                       | 0.52    | 7.0 (-4.1, 18.1)                                           | 0.21    |
| Total cholesterola - mg/dl
At baseline
At 3 months
Change (baseline to 3 months)        | 163.7 (142.9, 184.5)
164.8 (144.0, 185.6) | 172.0 (155.3, 188.8)
166.3 (149.5, 183.1) | 166.3 (148.6, 184.1)
167.1 (149.4, 184.8) | -3.6 (-16.8, 9.6)                                                       | 0.59    | 6.5 (-5.3, 18.4)                                           | 0.28    |
| Triglycerides# - mg/dl
At baseline
At 3 months
Change (baseline to 3 months)*           | 130.1 (93.5, 181.1)
137.5 (98.8, 191.4)   | 133.3 (102.0, 174.0)
139.1 (106.5, 181.7) | 132.8 (100.1, 176.1)
123.7 (93.2, 164.1)  | 93.3 (77.0, 113.0)                                                      | 0.48    | 89.2 (75.1, 106)                                           | 0.19    |

Strategy 1: In-store education only. Strategy 2: In-store education plus online training and tools. BMI: Body-mass index. Modelling process for each outcome described in Tables 3 and 4 for each endpoint. a Data represent least-squares means (95% CI). Intervention effect is difference in mean change in outcome and 95% confidence interval. # Modeling for triglycerides based on log-transformed data. Values for groups at all timepoints represent medians (geometric means) and confidence intervals. \* Values for comparisons (within and across groups) represent percentage of reference value and confidence intervals. Intervention effect is the relative risk and 95% confidence interval. Two-sided t-tests were used. No adjustments for multiple comparisons were made.

**Table S19: Pre-COVID-19 Subgroup Analyses at Baseline and 6 Months**

|                                                                                                                    | Control
(n=22)
Mean (95%CI)            | Strategy 1
(n=45)
Mean (95%CI)         | Strategy 2
(n=42)
Mean (95%CI)         | Primary Comparison (CI)
Strategies 1 and 2 vs. Control
(N=109) | P-value | Secondary
Comparison (CI)
Strategy 2 vs. 1
(N=87) | P-value |
|--------------------------------------------------------------------------------------------------------------------|----------------------------------------------|----------------------------------------------|----------------------------------------------|----------------------------------------------------------------------|---------|------------------------------------------------------------|---------|
| DASH Scorea
At baseline
At 6 months
Change (baseline to 6 months)                       | 45.1 (39.9, 50.4)
49.8 (44.5, 55.1)       | 42.6 (38.6, 46.6)
51.9 (47.8, 55.9)       | 42.7 (38.4, 47.0)
53.1 (48.8, 57.5)       | 5.1 (-0.8, 11.1)                                                     | 0.09    | 1.2 (-4.2, 6.6)                                            | 0.67    |
| Systolic blood pressurea - mm Hg
At baseline
At 6 months
Change (baseline to 6 months)  | 133.9 (123.3, 144.5)
129.2 (118.6, 139.9) | 134.1 (125.3, 142.9)
127.5 (118.7, 136.3) | 128.9 (119.3, 138.4)
124.9 (115.2, 134.5) | -0.6 (-8.8, 7.6)                                                     | 0.89    | 2.6 (-4.9, 10.0)                                           | 0.50    |
| Diastolic blood pressurea - mm Hg
At baseline
At 6 months
Change (baseline to 6 months) | 87.5 (80.2, 94.9)
83.6 (76.3, 90.9)       | 85.1 (79.0, 91.2)
80.2 (74.1, 86.3)       | 85.2 (78.6, 91.9)
83.3 (76.6, 90.0)       | 0.6 (-4.4, 5.5)                                                      | 0.82    | 2.9 (-1.6, 7.4)                                            | 0.21    |
| BMIa - kg/m^2
At baseline
At 6 months
Change (baseline to 6 months)           | 34.5 (28.2, 40.8)
34.4 (28.1, 40.7)       | 37.2 (32.0, 42.4)
36.6 (31.4, 41.8)       | 35.1 (29.3, 40.8)
34.3 (28.5, 40.0)       | -0.6 (-1.3, 0.1)                                                     | 0.11    | -0.2 (-0.9, 0.5)                                           | 0.58    |
| Non-HDL-Ca - mg/dl
At baseline
At 6 months
Change (baseline to 6 months)                | 113.0 (93.3, 132.7)
123.2 (103.5, 142.9)  | 122.3 (106.4, 138.2)
119.4 (103.4, 135.4) | 118.5 (101.7, 135.3)
120.8 (103.8, 137.8) | -10.5 (-26.3, 5.3)                                                   | 0.20    | 5.2 (-9.2, 19.7)                                           | 0.48    |
| Total cholesterola - mg/dl
At baseline
At 6 months
Change (baseline to 6 months)        | 163.7 (142.9, 184.5)
172.7 (151.9, 193.5) | 172.0 (155.3, 188.8)
168.6 (151.8, 185.5) | 166.3 (148.6, 184.1)
171.0 (153.1, 189.0) | -8.4 (-25.2, 8.5)                                                    | 0.33    | 8.1 (-7.3, 23.5)                                           | 0.30    |
| Triglycerides# - mg/dl
At baseline
At 6 months
Change (baseline to 6 months)*           | 130.1 (93.5, 181.1)
135.2 (97.2, 188.2)   | 133.3 (102.0, 174.0)
130.1 (99.5, 170.2)  | 132.8 (100.1, 176.1)
134.5 (101.1, 179.0) | 95.7 (74.6, 122.8)                                                   | 0.73    | 103.7 (82.6, 130.2)                                        | 0.75    |

Strategy 1: In-store education only. Strategy 2: In-store education plus online training and tools. BMI: Body-mass index. Modelling process for each outcome described in Tables S9, S12, and S13 for each endpoint. a Data represent least-squares means (95% CI). Intervention effect is difference in mean change in outcome and 95% confidence interval. # Modeling for triglycerides based on log-transformed data. Values for groups at all timepoints represent medians (geometric means) and confidence intervals. \* Values for comparisons (within and across groups) represent percentage of reference value and confidence intervals. Intervention effect is the relative risk and 95% confidence interval. Two-sided t-tests were used. No adjustments for multiple comparisons were made.

**Table S20: Change in DASH Score for Subgroups at 3 Months**

| Subgroup                | Strategies 1 and 2
Mean (95% CI) | Control
Mean (95% CI) | Absolute Mean DASH
Difference
(compared to Control)
Mean (95% CI) | p-value            |
|-------------------------|-------------------------------------|--------------------------|----------------------------------------------------------------------------|--------------------|
| Age                     |                                     |                          |                                                                            | Interaction: <0.01 |
| 21-50                   | 52.9 (49.6, 56.1)                   | 56.7 (51.5, 61.9)        | -3.9 (-10.4, 2.7)                                                          | 0.24               |
| 51-75                   | 56.6 (55.0, 58.2)                   | 50.2 (46.6, 53.7)        | 6.4 (2.5, 10.3)                                                            | <0.01              |
| Gender                  |                                     |                          |                                                                            | Interaction: 0.64  |
| Female                  | 55.8 (54.0, 57.5)                   | 52.9 (49.4, 56.4)        | 2.8 (-1.2, 6.9)                                                            | 0.17               |
| Male                    | 55.4 (52.9, 57.9)                   | 50.9 (45.3, 56.5)        | 4.5 (-1.7, 10.7)                                                           | 0.15               |
| Race                    |                                     |                          |                                                                            | Interaction: <0.01 |
| Not White               | 53.1 (50.4, 55.8)                   | 58.3 (52.1, 64.5)        | -5.2 (-12.0, 1.7)                                                          | 0.14               |
| White                   | 56.6 (55.0, 58.3)                   | 50.6 (47.3, 54.0)        | 6.0 (2.1, 9.9)                                                             | <0.01              |
| Married                 |                                     |                          |                                                                            | Interaction: 0.46  |
| Yes                     | 56.3 (54.5, 58.1)                   | 52.0 (48.2, 55.8)        | 4.3 (-0.1, 8.6)                                                            | 0.05               |
| No                      | 54.5 (52.1, 56.8)                   | 52.8 (47.8, 57.8)        | 1.7 (-4.0, 7.4)                                                            | 0.56               |
| Education               |                                     |                          |                                                                            | Interaction: 0.40  |
| Bachelor/Graduate       | 55.8 (54.0, 57.6)                   | 53.4 (49.5, 57.3)        | 2.4 (-2.0, 6.8)                                                            | 0.29               |
| Not                     | 55.4 (53.0, 57.7)                   | 50.0 (44.9, 55.1)        | 5.4 (-0.2, 10.9)                                                           | 0.06               |
| Employment              |                                     |                          |                                                                            | Interaction: 0.88  |
| Fulltime                | 54.4 (52.4, 56.5)                   | 51.3 (47.3, 55.4)        | 3.1 (-1.5, 7.8)                                                            | 0.19               |
| Not Fulltime            | 57.0 (55.0, 59.1)                   | 53.4 (49.0, 57.8)        | 3.6 (-1.3, 8.4)                                                            | 0.15               |
| Annual Household Income |                                     |                          |                                                                            | Interaction: 0.56  |
| < \$100,000             | 55.7 (53.7, 57.8)                   | 51.6 (47.9, 55.3)        | 4.1 (-0.1, 8.4)                                                            | 0.06               |
| ≥ \$100,000             | 55.5 (53.5, 57.6)                   | 53.5 (48.2, 58.8)        | 2.1 (-3.8, 8.0)                                                            | 0.49               |
| Household Size          |                                     |                          |                                                                            | Interaction: 0.53  |
| 1-2 People              | 55.6 (53.9, 57.3)                   | 52.9 (49.4, 56.4)        | 2.6 (-1.3, 6.6)                                                            | 0.19               |
| 3 or More               | 55.8 (53.2, 58.5)                   | 50.8 (45.0, 56.7)        | 5.0 (-1.7, 11.6)                                                           | 0.14               |

|                                                                                                                                                                                                                                                                                                                                                                                                                                                                                                                                                                                                     |                                        |                                        |                                     |                                    |
|-----------------------------------------------------------------------------------------------------------------------------------------------------------------------------------------------------------------------------------------------------------------------------------------------------------------------------------------------------------------------------------------------------------------------------------------------------------------------------------------------------------------------------------------------------------------------------------------------------|----------------------------------------|----------------------------------------|-------------------------------------|------------------------------------|
| Frequency of Cooking at Home
< 5-6x/week
≥ 5-6x/week                                                                                                                                                                                                                                                                                                                                                                                                                                                                                                                                          | 54.4 (52.4, 56.4)
57.1 (55.1, 59.1) | 51.4 (47.6, 55.2)
54.1 (49.0, 59.2) | 3.0 (-1.6, 7.5)
2.9 (-2.6, 8.4)  | Interaction: 0.98
0.20
0.30  |
| Activity level
Moderate/very
Less                                                                                                                                                                                                                                                                                                                                                                                                                                                                                                                                                             | 56.8 (55.1, 58.6)
53.7 (51.1, 56.2) | 51.6 (47.2, 55.9)
53.0 (48.9, 57.2) | 5.3 (0.6, 9.9)
0.6 (-4.4, 5.6)   | Interaction: 0.16
0.03
0.81  |
| Hypercholesterolemia
No
Yes                                                                                                                                                                                                                                                                                                                                                                                                                                                                                                                                                                   | 54.7 (52.2, 57.3)
56.1 (54.3, 57.8) | 53.5 (48.6, 58.4)
51.7 (47.7, 55.6) | 1.3 (-4.2, 6.8)
4.4 (-0.1, 8.9)  | Interaction: 0.37
0.65
0.05  |
| Hypertension
No
Yes                                                                                                                                                                                                                                                                                                                                                                                                                                                                                                                                                                           | 54.8 (52.2, 57.4)
56.0 (54.3, 57.8) | 58.9 (52.8, 64.9)
50.2 (46.8, 53.7) | -4.0 (-10.9, 2.8)
5.8 (1.9, 9.7) | Interaction: 0.01
0.25
<0.01 |
| Obese
No
Yes                                                                                                                                                                                                                                                                                                                                                                                                                                                                                                                                                                                  | 56.7 (54.5, 59.0)
55.0 (53.0, 56.9) | 55.8 (50.4, 61.2)
50.9 (47.2, 54.6) | 0.9 (-4.9, 6.8)
4.1 (-0.4, 8.6)  | Interaction: 0.40
0.76
0.08  |
| Baseline DASH Score
< 40
≥ 40                                                                                                                                                                                                                                                                                                                                                                                                                                                                                                                                                                 | 52.4 (49.9, 55.0)
57.3 (55.6, 58.9) | 48.1 (42.7, 53.6)
53.9 (50.5, 57.4) | 4.3 (-1.8, 10.4)
3.3 (-0.6, 7.2) | Interaction: 0.78
0.17
0.10  |
| Strategy 1: In-store education only. Strategy 2: In-store education plus online training and tools. DASH score at 3 months was modeled (dependent variable) with a separate ANOVA model for each subgroup - including treatment-group (Control, Strategies 1 and 2) and subgroup x treatment-group interaction as additional terms. Imputed data was used for missing DASH scores. Data represent least-squares means (95% CI). Test for interaction effect was a two-sided F-test. Tests for differences between groups was a two-sided t-test. No adjustments for multiple comparisons were made. |                                        |                                        |                                     |                                    |

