#### **f. Statistical Analysis**

A minimum of 250 adults will be randomized into the study. Approximately 100, 100, and 50 participants will be randomized to the in-store POP education arm, the combination online/in-store POP education arm, and the control arm, respectively (see section *Data Analysis and Data Monitoring* for power calculations and testing plan).

NDSR food data will be used to calculate overall diet quality using the DASH score. The DASH score is a modification of the DASH index developed by Gunther et al. [11]. DASH score is a continuous 90-point measure with higher scores equating to higher DASH diet adherence.

Randomization will use stratification to balance important baseline covariates among study groups. These covariates will be age, sex, and household size.

Data will initially be assessed for their distribution (e.g. normality) and the level of missing values. Descriptive statistics will be calculated for each arm. The primary endpoint will be the change from baseline to Day 90 in the DASH score (as assessed by dietary intake recalls). Using hierarchical testing, up to 2 tests will be performed:

- 1) First test: Any POP education arm vs. control arm
- 2) Second test: In-store POP education arm vs. combined online/in-store POP education arm

An intention-to-treat (ITT) analysis will be used for both tests. The “last observation carried forward” approach will be used for missing data. Ascertainment of DASH score at Day 90 for each participant will require completion of at least 1 of 3 dietary intake recalls. Sensitivity analyses may be performed using a “complete case” approach or multiple imputation techniques.

The primary comparisons will use an analysis of covariance (ANCOVA) model. This multivariable model, controlling for the baseline covariates, will have DASH score as the dependent variable with treatment arm as the independent variable. As part of this process, the normality of distribution of DASH scores at both baseline and Day 90 will be assessed. If necessary, transformations (e.g. log) will be used to satisfy the assumptions of the model. The primary treatment group comparisons will be performed using appropriate contrasts of the randomization arm estimates. Statistical testing will only be performed for the second test if  $p < 0.05$  is met for the first test (i.e. hierarchical testing). This will preserve an alpha-error of 0.05.

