### Overall Analysis Approach

Descriptive Statistics. Descriptive statistics will consist of mean and standard deviation (SD) and median and interquartile range (IQR) for variables. Counts and percentages will be used for categorical variables. Unless otherwise determined, descriptive statistics will be produced for all variables and all time-points.

Distributions/Transformations. Residuals from models will be examined for primary and key secondary outcomes for distributional properties, to ensure model assumptions (normality and independence of residuals) are met. If they are not met, data transformation or other analysis methods (e.g. nonparametric) will be used.

Treatment Groups. Subjects were randomly assigned to one of three treatment groups: 1) Control; 2) In-store Point-of-Purchase Education (POP1); and 3) Combined Online and In-store Point-of-Purchase Education (POP2). The designation POP1/POP2 will be used to denote the combining of data from POP1 with POP 2.

Primary Outcome and Comparison: The primary outcome is the DASH score. The primary comparison of interest is the change in DASH score between baseline and the 3-month follow-up.

Key Secondary Outcomes: The main secondary outcomes are BMI, SBP, DBP, non-HDL cholesterol, total cholesterol and triglycerides.

Modeling. The primary comparisons will use a mixed model for repeated measures. This multivariable model, controlling for covariates, will have DASH score as the dependent variable with treatment as the independent variable. The primary treatment group comparisons will be performed using appropriate contrasts of the treatment arm estimates.

Significance Level ( $\alpha$ ) and Tests. For the primary and key secondary endpoints, hierarchical testing will be used, first comparing Control vs. POP1/POP2. If  $p < 0.05$  for that test, then the two intervention groups will be compared (POP1 vs. POP2). This will preserve an alpha-error of 0.05. For all other endpoints, testing will be done at the  $\alpha = 0.05$  significance level, with no multiple comparison adjustments. All tests, unless otherwise noted, will be two-sided.

COVID-19 Impact Analysis. Due to the COVID-19 pandemic occurring during the course of the SuperWIN, we have a COVID-19 impact analysis following regulatory guidance, defined below.

Software. Unless otherwise specified, SAS® 9.4 TS1M5 (SAS, Inc., Cary, NC) software will be used for all analyses.

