# Subgroups of Interest: Primary Endpoint at 3 Mon

| Subgroup                                           | POP1/POP2 | Control | Absolute Mean DASH Difference
(compared to Control) |
|----------------------------------------------------|-----------|---------|--------------------------------------------------------|
| Age
21-50
51-75                              |           |         |                                                        |
| Gender
Male
Female                           |           |         |                                                        |
| Race
White
Not White                         |           |         |                                                        |
| Married
Yes
No                               |           |         |                                                        |
| Education
Bachelor/Graduate
Not              |           |         |                                                        |
| Employment
Fulltime
Not Fulltime             |           |         |                                                        |
| Annual Household Income
≥\$100,000
Less      |           |         |                                                        |
| Household Size
Single Person
More            |           |         |                                                        |
| Frequency of Cooking at Home
≥5-6x/week
Less |           |         |                                                        |
| Activity level
Moderate/very
Less            |           |         |                                                        |
| Hypercholesterolemia
Yes
No                  |           |         |                                                        |
| Hypertension
Yes
No                          |           |         |                                                        |
| Obese                                              |           |         |                                                        |

|                                              |  |  |  |
|----------------------------------------------|--|--|--|
| Yes
No                                    |  |  |  |
| Baseline DASH Score
Above ≥40
Below 40 |  |  |  |

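### The Table S20 subgroup analysis is labelled as change in DASH but models the 3-month score without baseline DASH, so three quotable interactions rest on small control subgroups with chance imbalance left uncorrected

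*Combined protocol and SAP*

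**What the plan says.** - **Primary endpoint.** Protocol section 5f: "The primary endpoint will be the change from baseline to Day 90 in the DASH score". SAP, Overall Analysis Approach: "The primary comparison of interest is the change in DASH score between baseline and the 3-month follow-up". The protocol analyses it by ANCOVA controlling for baseline covariates (it lists age, sex and household size). The SAP uses a mixed model for repeated measures controlling for covariates.
- **SAP subgroup table.** It is headed "Subgroups of Interest: Primary Endpoint at 3 Mon" and has a column for the absolute mean DASH difference from control. It gives no model, covariates or missing-data rule.
- **Table S20.** The title is "Change in DASH Score for Subgroups at 3 Months". The footnote reads "DASH score at 3 months was modeled (dependent variable) with a separate ANOVA model for each subgroup". The only further terms it names are treatment and its interaction with the subgroup; no other covariate is listed. On missing values it says "Imputed data was used for missing DASH scores", without stating the method.
- **Household size.** The SAP subgroup table splits one person from more than one. The SAP baseline table and Table S20 split one or two people from three or more.
- **Status.** Protocol section 5f calls the subgroup analyses exploratory. Table S20 states that no multiplicity adjustment was made.

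**The concern.** The table's title and the SAP heading lead a reader to expect subgroup effects on the primary endpoint. The table gives differences in the 3-month level instead. With only 46 controls, some control subgroups are very small, and a high 3-month mean in such a group may partly reflect a high starting level. The model described cannot distinguish the two, although baseline DASH was collected for exactly this purpose. Age, race and hypertension are the rows most likely to be quoted, because their interaction P-values are 0.01 or below and the effect changes sign between the two halves of each split.

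**Working it through.** **1. Do the printed figures fit an unadjusted 3-month model?** Yes, on three counts.
- Across all 14 splits, each printed difference equals the gap between the two printed 3-month means to within 0.1.
- Precision-weighting the two halves of each split returns almost the same arm means every time: intervention 55.6 to 55.9, control 52.2 to 52.5.
- In the baseline-DASH row, the 3-month means still differ between baseline ≥40 and <40 by 57.3 − 52.4 = 4.9 (intervention) and 53.9 − 48.1 = 5.8 (control). Baseline therefore predicts the outcome, and no continuous baseline term appears to have absorbed it.

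**2. Reproducing the interaction tests.** Inputs are the Table S20 differences and 95% intervals. SE = (upper − lower)/(2 × 1.97). Contrast SE = √(SE₁² + SE₂²). t = contrast/SE on 243 df. The last column is contrast − 1.97 × SE: the movement towards zero, at fixed SE, that would take P above 0.05.

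| Split | Differences | SEs | Contrast | Contrast SE | t | P (printed) | Shift that removes P<0.05 |
|---|---|---|---|---|---|---|---|
| Age | −3.9, 6.4 | 3.32, 1.98 | 10.3 | 3.87 | 2.66 | 0.008 (<0.01) | 2.7 |
| Race | −5.2, 6.0 | 3.48, 1.98 | 11.2 | 4.00 | 2.80 | 0.006 (<0.01) | 3.3 |
| Hypertension | −4.0, 5.8 | 3.48, 1.98 | 9.8 | 4.00 | 2.45 | 0.015 (0.01) | 1.9 |

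The hypertension result agrees with the printed value within the rounding of the intervals.

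**3. Size of the control subgroups.** With a common SD, n is proportional to 1/SE², scaled to 46 controls. For age, the control intervals 51.5 to 61.9 and 46.6 to 53.7 give SEs of 2.64 and 1.80, hence about 15 and 31 people. The same step gives about 10 and 36 for race (not White, White) and about 11 and 35 for hypertension (no, yes).

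**4. Where the contrasts come from.** Mostly from the control arm. The gap between the two control means is 56.7 − 50.2 = 6.5 for age, 58.3 − 50.6 = 7.7 for race and 58.9 − 50.2 = 8.7 for hypertension, out of contrasts of 10.3, 11.2 and 9.8.

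**5. How large could chance baseline imbalance be?** For age, the SE of the imbalance in the contrast is SD × √(1/14.6 + 1/31.4 + 1/39.2 + 1/161.8) = 0.363 × SD. The baseline SD within these subgroups is not given. Assuming 8 to 12 points, the SE is 2.9 to 4.4 points. The effect on the contrast is slope × imbalance. The slope is 1 for a change-score contrast and smaller when baseline is a covariate: at an assumed slope of 0.5, a 2.7-point shift needs an imbalance of 2.7/0.5 = 5.4 points.

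**6. Illustration from Table S18 (pre-COVID subset).** Baseline: (42.6 + 42.7)/2 − 45.1 = −2.45. Three-month level: (53.2 + 56.4)/2 − 48.9 = 5.9. Change: 5.9 + 2.45 = 8.35, printed as 8.3. With assumed baseline slopes of 0.25, 0.5 and 0.75, the adjusted difference would be 6.5, 7.1 and 7.7.

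**The case against.** The strongest reply is that the arms were randomised. Within a subgroup defined at baseline, the 3-month difference and the difference in change estimate the same effect in expectation. Chance imbalance is already reflected in the wide intervals, and the interaction test remains valid. That stands. A reader might infer that the three interactions are biased or are artefacts of baseline differences. The documents do not show that: they give no baseline DASH by arm within these subgroups, and adjustment could move a contrast either way.

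A reader might also take the pre-COVID gap between 5.9 and 8.35 as the size of the error in Table S20. It is not. It comes from another subset and model and is the full slope-1 shift. Overall, Table S20 moves little when baseline is accounted for coarsely: the precision-weighted difference is 3.6 in the baseline-DASH row and 3.3 in the gender row. That does not exclude larger shifts in a control subgroup of 10 to 15.

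Three further inferences fail. The footnote does not say that imputation was single or by last observation carried forward; that rule is in the protocol, not in Table S20. The rows cannot be said to miss the whole-trial effect, because the documents supplied do not print the whole-trial 3-month change effect. And baseline DASH is not wholly absent, since one of the 14 models contains it dichotomised.

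Finally, the SAP column does ask for an absolute DASH difference, DASH score is the named dependent variable in both primary models, and the ANOVA appears in a results footnote rather than in the plan. So the departure is partly one of labelling. The SAP's own gap is that it specifies no subgroup model.

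**Conclusion.** The point holds in limited form. Table S20 is mislabelled, and its model leaves out baseline DASH in 13 of 14 splits and the primary-model covariates except where one of them is the subgroup. It therefore does not match the change-from-baseline endpoint, and the SAP prespecified no subgroup model. The cost is uncorrected chance imbalance and lost precision, not bias in expectation. It matters most for age, race and hypertension, where a baseline-driven shift of about 2.7, 3.3 or 1.9 points would remove P<0.05. For age, that is no larger than one standard error of chance imbalance if the contrast is on change (slope 1); with baseline as a covariate, the imbalance needed is larger. These figures rest on back-solved subgroup sizes, an assumed baseline SD of 8 to 12 and unchanged standard errors. Whether the interactions would survive adjustment cannot be determined from the documents. The primary test is unaffected.

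**What to change.** In the SAP, specify the subgroup model and rerun Table S20 with it. Add subgroup and treatment-by-subgroup terms to the primary analysis: either the repeated-measures model with contrasts on change, or 3-month DASH with continuous baseline DASH and the primary-model covariates. The second form also recovers precision; a change contrast need not. Use the primary missing-data approach and name it. By Table S9, 4 + 8 + 10 = 22 of 247 participants lacked 3-month dietary intake. Report baseline-adjusted differences and interaction tests, title the table to match, and use a single household-size cut in the SAP subgroup table, the SAP baseline table and Table S20. If the table is not rerun, it should at least be retitled as an unadjusted 3-month DASH score. The cost is one table and a few lines of SAP text; some interactions may weaken.
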